#### Secondary outcome

The occurrence and time to onset of any subsequent mood disorder and/or depressive episode are secondary outcomes. Recurrence of MDD and related mood disorders will be assessed by diagnostic interview (KSADS-PL) administered by IEs at post-intervention and at 12 months.

Dose is a rating of homework completion and skill integration (rated by the clinician), and degree of rumination change (defined by RCI). The primary clinical outcome is therefore change on the RRS score (as captured by the RCI) after treatment. We will additionally examine the stability of RRS change at 6 and 12 months post-intervention.

### Data collection and management

To promote participant retention, the study coordinators will keep in contact with the families via their preferred method (e.g., text messaging, emailing, and telephone calls). The participant payment schedule will be spread out across visits, so that adolescents will be compensated for each time they attend an assessment. Follow-up appointments will be scheduled in advance and at the families’ convenience, and participants will be contacted before appointments to remind them of the appointment and confirm the date/location. In the event of a missed visit, participants will be contacted through email and telephone. We will then wait until the next assessment/visit and attempt to schedule the participant. If the participant is unresponsive after several missed visits without a response, they will be called directly by co-PI [name]. They will be asked if they wish to discontinue or if no response, they will be considered lost to follow-up. To enhance interest and retention, additional strategies will be employed, including sending a birthday postcard (if agreed), provision of a printed 2d picture of the adolescent’s brain (after the intervention period, if agreed), and a 3D model of the adolescent’s brain (at 12 month follow-up, if agreed).

The MRI data will be stored in mirrored RAID (redundant array of independent disks) arrays, which are both firewall-protected and isolated from access outside the immediate local network. The RAID arrays will also be used to store other data from the participants, and will be backed up daily with digital tape. All non-image subject data will bestored in REDCap. REDCap is a meta-data driven software solution that facilitates secure collaborative data access, real time data validation and auditing [89], and is compliant with the Health Insurance Portability and Accountability Act (HIPAA) and General Data Protection Regulation (GDPR) best practices [90, 91].

All data will be collected, stored and handled in accordance with HIPAA [90]. The study protocol, documents, data management, and safety plans have been approved by the University of Utah Institutional Review Board (IRB_00113733). Approval for sharing and analysis of deidentified and coded data has been obtained by the University of Exeter Psychology Ethics Committee and data sharing plans have been subject to ethical review to ensure these are compliant with the European Union GDPR [91]. It will be made clear to participants how their data will be used and stored prior to obtaining consent to participate in the trial. All participants will be assigned a unique ID; coding all study data and images with an identifying number and referring to this number in all analyses will preserve confidentiality. The participants will not be identified in any reports of behavioural, clinical, or functional data.

Two independent clinicians with expertise in cognitive behavioural therapy and in working with adolescents, as well as an independent statistician at Utah, compose the internal Data Safety and Monitoring Board (DSMB), which will meet in person at least once per year for routine review of records (review of protocol, of a prototypic record, review of all adverse events, and review of all protocol deviations), and at least every 6 months by telephone/videoconference, if there are any actionable items that occur for enrolment or conflict of interest concerns, or participant safety review. The Independent Study Monitor (ISM) ([name], M.D., adolescent psychiatrist), in concert with the DSMB, will set up a study charter before enrolment of the first participant that includes enrolment data, safety data, and data integrity. The DSMB will review de-identified study data for data quality and integrity, adherence to the protocol, participant safety, study conduct and progress twice per year. The ISM and DSMB will be blinded to participant group assignment. In the case of specific incidents (expected or unexpected adverse events), the ISM or DSMB may request from the study team information pertaining to group assignment for a given individual, or aggregate information on a group of individuals who experienced an adverse event. The ISM and DSMB retain autonomy to make determinations and recommendations in the case of adverse events. As the treatments have already been used with adolescents in a pilot study and in a larger European trial [66–68], such modifications are not anticipated. The ISM or DSMB will issue a monitoring report to the PI following each review/meeting, including any significant actions taken and any final recommendation(s) with regard to the study’s continuation. The ISM will be responsible for reviewing trial stopping/pausing decisions and enrolment recommendations. The ISM will review, within 24 h, any suicide-related assessments or concerns. In cases with re-emerging depression without increased suicidal ideation, the ISM will be consulted after two consecutive elevated measurements and will then decide how the participant shall proceed. The participant may be asked to pause participation, in which cases referrals will be made to suitable clinical services. At such a time as when the adolescent is stable and low risk, they may resume participation in the trial. There are no anticipated stopping rules for the entire study. The intervention is a low-risk intervention in those who are currently low in symptoms, and families can pursue treatment as usual during the trial.

### Statistical methods

Primary analyses will be conducted on intention-to-treat basis (as randomised) and missing data assumed to be missing at least at random (MAR), confirmed using missing data analysis. Unplanned missing data will be handled via multiple imputation (MI). Secondary variables will be used to improve the estimation of missing data. Sensitivity analysis, assuming a variety of MI models (Missing at Random; Missing Not at Random), will confirm the probable impact of missing data.

To compare the effects of RFCBT with the control arm, mixed-effects longitudinal models will be used. The first analysis tests change in RRS scores; the second analysis tests change in connectivity between the left posterior cingulate cortex and right inferior frontal gyrus. For each, the random subject intercept parameter will explain the variation in measurements of subjects at baseline, whereas the random slope parameter will explain variation over time. The models will also incorporate within-subject variation. The group by time interaction parameter will be used to differentiate the trend of RFCBT from that of the control arm on each outcome. Sustainability of improvement will be measured utilizing data from post-intervention to until 12 months post-intervention. To measure relation between degree of daily engagement in homework and degree of reduction in rumination, we will calculate Pearson correlations. A contrast using pre and post measures of rs-fMRI between left PCC and right IFG in adolescents on the RFCBT arm will be compared to the control arm, as described in Jacobs et al. 2016 [57]. The same approach will be adopted for exploratory, task-based fMRI, capturing state rumination.

Preliminary data and published studies include targeted seed-based analyses of connectivity between PCC (DMN node) and left inferior temporal gyrus (CCN node) [46, 47, 58, 60, 62, 64–69]. Connectivity of PCC to inferior frontal gyrus (also CCN) was considered. Because rs-fMRI analyses are rapidly evolving, there may be additional analytic strategies that evolve between now and interim study analysis – we will co-publish any use of these new techniques in the same paper with the primary seed-based analysis. We will evaluate and publish a Bayesian technique to allow for subtle variations in seed and node 3D coordinates. This is based upon observed sample to sample fluctuations in spatial smoothing, functional connectomic parcels, such that exact coordinates may not align for seed and node from sample to sample. As an example, our prior work shows similar, and only partially overlapping nodes for identification of PCC to superior frontal gyrus increased connectivity in MDD compared to healthy controls in three independently published samples [46].

Subsequent analyses will use the Complier Average Causal Effect (CACE) analysis [92, 93]. CACE assumes that the effect of treatment depends on the adherence to treatment (dose effects), which in turn is dependent on randomisation, and that randomisation has no direct effect on the outcome variable. As such, CACE takes into account adherence and compliance with the treatment in order to estimate a treatment effect, whilst also retaining the benefits of randomisation. Briefly, CACE estimates the difference in the outcome variable between the compliers in the treatment arm and the compliers in the control arm had they been offered the treatment, assuming that there are similar rates of compliance in both arms as a result of randomisation. Compliance will be defined as attending at least 8 out of a possible maximum of 16 RFCBT sessions.

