## Methods

### Study design

The study consists of a two-arm parallel-group single-blind randomised controlled trial. Stage 1 compares RFCBT to TAU + AO; stage 2 compares RFCBT to TAU + relaxation. The assessment team members will be blind to treatment arm. Our primary hypotheses are that RFCBT will be superior to the control arm in reducing (a) rumination, and (b) rs-fMRI connectivity between DMN and CCN. Our secondary hypotheses are that (a) that RFCBT will be superior to the control arm in reducing recurrence of depression over 12 months; and (b) engagement with RFCBT homework (dose response) will be related to changes in (i) rumination, (ii) DMN and CCN resting state connectivity, and (iii) degree of change in regional brain activation during a rumination induction from pre- to post- treatment. The study design was published in the National Clinical Trials Website (NCT03859297) in March 2019. The only substantive change is the move to tele-assessment and teletherapy in March 2020 in response to the COVID-19 pandemic. The neuroimaging protocol was discontinued from March through June 2020, and then reinstated with COVID-19 safety precautions.

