### Sample size

This trial was funded as the first stage (R61 grant) in a potential two-stage study, with the second stage (R33 grant) comparing RFCBT to an active control of relaxation therapy. Moving to the second stage is contingent on the first stage meeting the Go criteria of baseline to post-intervention between-treatment arm effect size changes of .5SD (effect size) in RRS and .5SD (effect size) in rs-fMRI connectivity from left PCC to right IFG. These effect sizes were chosen to reflect a noticeable clinical difference, necessary to progress to second stage. For this stage, the target recruitment is *n* = 30 per group. Power was computed using gPower 3.1 for a repeated measurements model in the first stage (R61), to compare the effects of RFCBT versus TAU + AO where observations are nested within subjects, targeting a .5SD (effect) size change, and with known reliability of RRS (*r* = .77) and rs-fMRI connectivity of left PCC to right IFG (*r* = .71). On this basis, a target recruitment of *n* = 30 per treatment arm is estimated to provide power of .99 for RRS and .98 for rs-fMRI. Assuming up to 15% follow-up attrition at post-intervention follow-up, power remains >.94 for both comparisons. For the R33 stage, there will be an active treatment comparator so the effect size difference is likely to be smaller. To achieve adequate power to detect a meaningful clinical difference, we assumed a minimum difference of 0.22 SD for each comparison; for power at 0.80, alpha at 0.05, assuming 15% follow-up attrition, we need to recruit 60 young people per treatment arm (*N* = 120).

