### Randomisation and allocation concealment

Block randomization will be performed using Matlab to produce computer-generated random codes that are stratified according to key clinical indicators and demographic variables, including RRS, CDRS, sex and age. Block randomization will be conducted by individuals ([name], [name]) who will not share rumination scores, be providing therapy, or conducting independent assessments and will therefore be independent of the assessment and treatment staff. After each of four waves, the effect of randomization on age, sex distribution, RRS score, and proportion randomized to each arm are evaluated, and the formula is adjusted to maximize equivalence of the two groups.

The independent evaluators (IEs) who conduct diagnostics at baseline and follow-up visits will have separate calendars and channels of contact from the therapists and coordinators. Assignment of therapist will be based upon mutual alignment of schedules of the adolescent and therapist. When more than one therapist is available in an aligned slot, therapist caseload and adolescent preference (male or female therapist) will be taken into consideration. IEs who complete evaluations (for presence of mood disorder, mood symptoms) after the assessment period will remain blinded to treatment. We will report the extent to which this is successful, and the proportion of post-treatment evaluations that are conducted by blinded IEs.

IEs will administer the intake baseline assessment, the post-treatment assessment (16-20 weeks following baseline), as well as subsequent 12 month post-intervention follow-up interviews. Between the baseline and post-treatment assessment, adolescents will additionally report bi-weekly RRS measurements that are not shared with the therapist. To avoid accidental unblinding of IEs, a research assistant will meet with the participant and legal guardian prior to each diagnostic evaluation, in order to remind them of the importance of not disclosing this information to their assessor. Fidelity of blinding will be monitored with a blindness questionnairecompleted by IEs during follow-up assessments as noted above.

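### The homework association with rumination is a Pearson correlation without baseline adjustment, and is biased if engagement is related to baseline RRS

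*Protocol article*

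**What the plan says.** The Study design section of the protocol article lists as secondary hypothesis (b) that "engagement with RFCBT homework (dose response) will be related to changes in (i) rumination", followed by connectivity and task activation. For rumination, the Statistical methods section names one analysis: "To measure relation between degree of daily engagement in homework and degree of reduction in rumination, we will calculate Pearson correlations". It mentions no baseline value or other covariate.

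Three other places bear on this:

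- **Change score.** The Secondary outcome section defines rumination change by the RCI. The Primary outcome section describes the RCI as allowing for measurement error, reliability and regression to the mean. Neither gives a formula.
- **Dose.** The sentence in the Secondary outcome section that defines dose lists clinician-rated homework completion and skill integration, and then the degree of rumination change.
- **Data at hand.** RRS and CDRS-R are taken at the baseline visit to decide eligibility (Recruitment). Between baseline and post-treatment, "adolescents will additionally report bi-weekly RRS measurements that are not shared with the therapist" (Randomisation and allocation concealment). An electronic diary records homework practice (Interventions).

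**The concern.** A reduction is baseline minus follow-up, so it carries the baseline score with it. Adolescents who start higher tend to fall further, whatever they practise. If engagement also varies with starting rumination, an unadjusted correlation mixes that shared dependence on baseline with any effect of practice. The hypothesis is labelled a dose response, so a reader would be inclined to credit the whole correlation to homework. Baseline RRS is available for everyone, so the plan accepts this without need.

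There is a second weakness. If dose includes rumination change, as the Secondary outcome section can be read, then correlating dose with rumination change is partly circular.

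**Working it through.** **1. The plan's own figures.** The protocol gives no power or precision for the homework correlation. Its stage 1 figures, "a target recruitment of *n* = 30 per treatment arm is estimated to provide power of .99 for RRS and .98 for rs-fMRI" and "Assuming up to 15% follow-up attrition at post-intervention follow-up, power remains >.94 for both comparisons", concern the between-arm comparison. A repeated-measures interaction with λ = f²·N·m/(1 − r), f = 0.5/2 = 0.25, m = 2 and alpha 0.05 gives:

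- N = 60: 0.9999 (r = .77) and 0.999 (r = .71), within 2 points of the stated values;
- N = 51: 0.999 and 0.996, consistent with the post-attrition statement.

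This recomputation enters the reliabilities as pre-post correlations. The same use of .77 is made below.

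**2. Sample size in the RFCBT arm.** Stage 1: 30, or 30 × 0.85 = 25.5 after attrition. Stage 2: 60, or 60 × 0.85 = 51.

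**3. Baseline and reduction.** With pre-post correlation r and post/pre SD ratio s,

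corr(baseline, reduction) = (1 − r·s) / √(1 + s² − 2·r·s).

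At s = 1 this is √((1 − r)/2) = √(0.23/2) = 0.34. The SD ratio is not given. At s = 0.8 the value is 0.60, and at s = 1.2 it is 0.10.

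**4. What passes to the homework correlation.** With no dose effect, the spurious correlation is corr(homework, baseline) × corr(baseline, reduction). The first factor is not in the documents, so a range is assumed. The type I error is simulated with normal data, s = 1 and a two-sided 0.05 test; the protocol does not state sidedness.

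| Assumed corr(homework, baseline) | Spurious r | Type I error, n = 30 | Type I error, n = 51 |
|---|---|---|---|
| 0 | 0 | 5.0% | 5.0% |
| 0.2 | 0.07 | 6.5% | 7.7% |
| 0.3 | 0.10 | 8.4% | 11.0% |
| 0.5 | 0.17 | 14.6% | 22.3% |

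Negative assumed values reverse the sign of the spurious r. At 0.3, letting s run from 1.2 to 0.8 moves the spurious r from 0.03 to 0.18.

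**5. Does the RCI remove it?** Dividing change by a constant cannot alter a Pearson correlation. In one simulated sample of 30, the correlation was 0.394 with raw change and 0.394 with the ordinary RCI. An index that shrinks baseline toward the mean by the reliability (0.77 × baseline − post, up to a constant) brings the spurious part to 0 in large simulated samples.

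**6. Against sampling error.** The 95% half-width around zero is tanh(1.96/√(n − 3)): 0.36 at n = 30 and 0.28 at n = 51. The bias does not shrink as n grows, so it counts for relatively more in stage 2.

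**7. After adjustment.** Adjusting for baseline RRS takes the spurious part to 0 under the model of step 4. With one covariate at n = 30, the critical |r| rises from 0.361 to 0.367. With two (26 df, t = 2.056) it is 2.056/√(26 + 2.056²) = 0.374.

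**The case against.** The strongest objection is that the protocol never says raw reduction is correlated. It defines change by an RCI that it describes as dealing with regression to the mean. If that index is regression-corrected, the coupling is gone. This stands as a limit on the point, but it does not settle it: without a formula the usual RCI is the natural reading, and step 5 shows that the usual RCI leaves the problem intact.

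A reader might infer several stronger things that the documents do not support:

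- **That baseline severity necessarily distorts the result.** Baseline enters the change score, but the homework correlation is biased only if engagement tracks baseline. The documents give no figure for that. If adolescents who ruminate more do less homework, the bias works against finding a dose response.
- **That selecting on elevated RRS makes matters worse.** Selection shifts the mean fall, but a narrower baseline range weakens the coupling. With the slope of 0.77 kept and the baseline variance halved (an assumption), it is 0.23·√0.5 / √(0.23²·0.5 + 0.407) = 0.25, down from 0.34.
- **That the small sample condemns the Pearson correlation.** The range of 25 to 30 is stage 1 only, and a cross-sectional regression meets nearly the same limit.
- **That time order is ignored throughout.** The Interventions section says the diary is meant to relate practice to everyday rumination, and the correlation is not said to be the only use of those data. Even so, no lagged analysis is named.

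The complier average causal effect analysis does not answer the point, because it defines compliance by sessions attended. A separate analysis plan may add covariates to this secondary analysis. However, the article does not leave the method open; it names one.

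**Conclusion.** The point holds as a minor one. The stated analysis is exposed to a bias of about 0.07 to 0.10 in the correlation if engagement correlates 0.2 to 0.3 with baseline RRS, and to none if the two are unrelated. The sign follows that of the homework-baseline correlation. These figures assume a pre-post correlation of .77, equal SDs and an ordinary RCI. At stage 1 size the bias is well inside the sampling error, so it would rarely decide the result alone. The case for change is that a better analysis is available from data already collected, at almost no cost. The wording that places rumination change inside dose should be corrected whichever RCI is used.

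**What to change.** - Replace the Pearson correlation with a regression of post-intervention RRS on homework engagement within the RFCBT arm, adjusted for baseline RRS and baseline CDRS-R. Report the coefficient with a 95% confidence interval, as an association. Adjustment handles the measured baseline scores, not every reason why some adolescents practise more.
- Define dose as homework and skill practice only, and use that definition in both the Secondary outcome and Statistical methods sections.
- State the RCI formula wherever the index is kept.
- Optionally, add a within-person mixed model in which diary practice in one interval predicts the next bi-weekly RRS. This addresses whether practice precedes improvement.

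No new data are needed. The cost is one or two degrees of freedom and slightly more analysis.

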#### Primary outcome

The primary treatment outcome is self-reported reductions in rumination, as assessed using the brooding scale of the RRS [36] from baseline to 16-20 weeks post-baseline. Brooding is defined as “passive and judgmental pondering of one’s mood” ([85], p. 99), and is associated with maladaptive strategies and depression. We will use the Reliable Change Index (RCI) as an indication of change in brooding rumination scores [86]. RCI is a measure of how much change in a measurement can be ascribed as a meaningful movement at a statistical level, for the individual case, based upon the error inmeasurement, reliability of an instrument, and moderating for the effects of regression to the mean. In pilot work with adolescents, 57% of those treated with RFCBT obtained a change in total rumination scores at or above an RCI level, suggesting an adequate dose of targeted therapy (vs. 14% of AO group, e.g., random reduction).

The primary brain target (capturing the neural mechanisms compensating for rumination as a result of RFCBT) is elevated connectivity between the DMN and CCN (and diminished within-CCN connectivity) during rs-fMRI [46, 87]. Resting state fMRI (rs-fMRI) will investigate concurrent (or synchronized) changes in blood flow while adolescents are at rest with eyes open looking at a fixation cross. All adolescents will complete two identical MRI scans: at baseline and then at post-intervention (16 weeks), corresponding to the end of RFCBT sessions. A 64-channel coil will be used, and rs-fMRI sequences will be consistent with the Adolescent Brain Cognitive Development (ABCD) study protocol, with same TR, TE, and multiband sequences. We will collect 4 rs-fMRI runs at each of the two scans. Seed-based analyses will be used to probe changes to functional connectivity. The primary neural outcome is therefore reduced rs-fMRI connectivity between the left posterior cingulate cortex and right inferior frontal gyrus (nodes within the DMN and CCN respectively) [57]. Network-based analysis will also be probed for CCN-DMN changes in connectivity. Two experimental task-based paradigms [63, 88] will be employed to investigate directed induced rumination vs. distraction (block design), and uninstructed use of rumination during a sustained attention task [63]. These probes are explicitly designed to look at network function and dynamics of DMN nodes alone and with CCN, and how they may change selectively with RFCBT.

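### The neural primary outcome has two analysis statements and no named deciding estimate, and the .5 SD Go rule does not say which estimate or which SD it uses

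*Protocol article*

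**What the plan says.** All references are to the Protocol article.

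- **Statistical methods, mixed model.** After the rumination analysis, "the second analysis tests change in connectivity between the left posterior cingulate cortex and right inferior frontal gyrus". The model has random effects: "the random subject intercept parameter will explain the variation in measurements of subjects at baseline, whereas the random slope parameter will explain variation over time". Its test is stated for both outcomes: "The group by time interaction parameter will be used to differentiate the trend of RFCBT from that of the control arm on each outcome".
- **Statistical methods, contrast.** Further on, after the follow-up and homework analyses, the text returns to the same connection: "A contrast using pre and post measures of rs-fMRI between left PCC and right IFG in adolescents on the RFCBT arm will be compared" with the control arm, following a cited earlier study. The same approach is then extended to exploratory task fMRI.
- **Statistical methods, analysis set.** "Primary analyses will be conducted on intention-to-treat basis (as randomised"), and "Unplanned missing data will be handled via multiple imputation (MI"). Neither rule is confined to one model.
- **Primary outcome.** "All adolescents will complete two identical MRI scans: at baseline and then at post-intervention (16 weeks"), so connectivity has two occasions per participant.
- **Sample size.** Stage 2 depends on "between-treatment arm effect size changes of .5SD (effect size) in RRS and .5SD (effect size) in rs-fMRI connectivity from left PCC to right IFG". Neither the estimator nor the SD is named. Power is given as .98 for connectivity with 30 per arm and a reliability of .71, and as above .94 after up to 15% attrition.

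**The concern.** Connectivity is one of two primary outcomes and one of two conditions for moving to Stage 2. The article describes its analysis twice and does not link the descriptions. A reader cannot tell whether the contrast is the imaging form of the group-by-time test or a further analysis, or which result would be reported as the primary neural finding.

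The Go rule adds a second gap. An effect of .5 SD has no fixed meaning until the SD is named. A change analysis naturally offers two candidates: the SD of connectivity at baseline and the SD of the change. If the choice is made after the data are seen, the same result can fall on either side of the line.

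**Working it through.** **Inputs.** From Sample size: 30 per arm, r = .71, up to 15% attrition (25.5 per arm), effect .5 SD. Assumed: two-sided alpha .05 (the article gives .05 for Stage 2 only), normal data with equal SDs, .71 taken as the pre–post correlation, and loss of second scans at random unless stated otherwise.

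**1. The plan's own power figure.** For a repeated-measures group-by-time test with m = 2 occasions, the noncentrality is λ = f²·N·m/(1 − r).
- f = .25, N = 60: λ = .0625 × 60 × 2/.29 = 25.9, power .999.
- f = .20, N = 60: λ = .04 × 60 × 2/.29 = 16.6, power .979, close to the stated .98.
- A between-arm difference in change of .5 baseline SD has cell effects of .5/4 = .125, so f = .125: λ = 6.47, power .706 at N = 60 and .632 at N = 51.

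The stated figure is therefore roughly reproduced, but not on the scale of a .5 baseline SD difference in change. It does not settle which SD the Go rule means.

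**2. Do the two analyses differ?** With two occasions, the group-by-time coefficient is (post − pre in RFCBT) − (post − pre in control), which is the between-arm difference in mean change. On one simulated complete data set, both gave an estimate of −0.5574 and a test statistic of −2.845. Two scans cannot separately identify a random intercept, a random slope and residual variance, so the connectivity model needs a constraint. In that data set, adding the random slope left the interaction estimate unchanged.

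**3. If the contrast were limited to participants with both scans.** Comparison with a two-occasion likelihood model that keeps baseline-only participants, 8,000 trials per row, true effect .5 baseline SD:

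| Missing second scans | p < .05 verdict differs | Go reading differs |
|---|---|---|
| none | 0.4% | 0% |
| 4 of 30 per arm, at random | 4.2% | 4.5% |
| 4 of 30 per arm, related to baseline in both arms | 3.2% | 3.5% |
| 15% setting, related to baseline in one arm only | 8.0% | 8.9% |

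In the last row, the both-scans contrast averages .45 instead of .50.

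**4. Scale of the Go rule.** SD of change = √(2(1 − .71)) = √.58 = .762 baseline SD.
- Scaled by the SD of change, the .5 line is met by a true effect of .5 × .762 = .38 baseline SD.
- A true .5 baseline SD becomes .5/.762 = .657 on that scale. With 25.5 per arm, the standard error is about √(2/25.5) = .28, so the chance of passing is Φ((.657 − .5)/.28) = Φ(.56) ≈ .71.
- In baseline SD units, the same true effect sits on the line and passes in about .50 of trials.

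**5. Efficiency.** An unadjusted change analysis has variance proportional to 2(1 − r) = .58. With baseline as covariate it is 1 − r² = .496. The ratio is (1 + r)/2 = .855. In 20,000 simulated trials with a true .5 baseline SD, power was .63 (change) and .69 (baseline-adjusted) with 15% missing, and about .70 and .76 with complete scans. Both methods used the same participants, so the gain comes from the adjustment and not from handling missing scans.

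**The case against.** The strongest reply is that there is only one analysis. With two scans, the interaction is the difference in change, and the contrast sentence may simply describe how the imaging software carries out the second analysis. The text also leans toward the mixed model: it introduces that model as the means of comparing the arms, and Sample size computes power for a repeated-measurements model. This largely stands. On complete data nothing turns on which statement is read.

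A reader might infer that the contrast is a completer analysis in conflict with the intention-to-treat rule. The article does not say so. It does not limit the contrast to participants with both scans, and its imputation rule is general, so a contrast on imputed data needs no observed second scan. The cited study's procedure cannot be checked here.

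A reader might also compare the contrast with a baseline-adjusted analysis, find that they disagree in 12–13% of trials, and blame the missing scans. That would be a mistake. The same comparison gives 11.5% (significance) and 12.5% (Go) with no missing scans, so the disagreement reflects change score against covariate adjustment. The article does not specify a baseline-adjusted model.

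It is also fair to say that the choice of SD affects the mixed-model estimate as much as the contrast, so it does not follow from having two statements. It is a gap in the Go rule itself. Finally, ranking analyses is often left to the analysis plan, and a request for a ranking alone would carry little weight.

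**Conclusion.** The point holds in a limited form. The article describes the analysis of the neural primary outcome twice without saying how the statements relate or which decides, and it ties the Go rule to neither an estimate nor an SD. The two statements alone have little numerical effect: none on complete data, and about 4–5% of Go readings at 15% missing, provided the contrast uses only participants with both scans and loss is similar in both arms. The figure is about 9% if loss depends on baseline in one arm only.

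The larger effects are scale and efficiency. At a true .5 baseline SD with 15% missing, the Go pass rate is about 71% or about 50% depending on the SD used, and power is .63 without baseline adjustment and .69 with it. These figures rest on r = .71 being the pre–post correlation, on normal data and on two-sided alpha .05.

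The documents do not support the stronger conclusion that the primary analysis breaks its own intention-to-treat rule or that two competing primary tests inflate the error rate. The change proposed below is a free improvement and does not repair an invalid analysis.

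**What to change.** State in the protocol and the analysis plan that one estimate serves both the primary neural test and the Go rule:

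- **Estimate:** the between-arm difference in left PCC–right IFG connectivity at the post-intervention scan, adjusted for baseline connectivity.
- **Participants:** all randomised, with the imputation already planned.
- **Scale:** baseline SD units for the .5 SD Go rule.
- **Contrast:** keep the pre/post contrast, label it supportive, state its analysis set, and say that it cannot replace the deciding estimate.

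This goes beyond labelling, because the group-by-time interaction is replaced by a baseline-adjusted comparison for this outcome. It also avoids the random intercept and slope that two scans cannot separate. If the investigators prefer the interaction, naming a constrained version and the baseline SD would still remove the ambiguity, but not gain the power. The cost is a few sentences. No new data or scans are needed, and the contrast is still run and reported.
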